### Participant randomization and study sample size

This study is at RCT. The randomization sequence is computer generated and used to randomize individuals to one of two study groups: intervention or control. A stratified randomization technique will be used to ensure equivalent 1:1 allocation of study conditions across three gender groups (male/trans male; female/trans female and other, which includes those who identify as two-spirited, bi-gendered, crossdresser, genderqueer, or for whom none of these options apply), and three age groups (i.e. 14–17, 18–21, and 22–26). Within each age/gender strata, participants will be randomized in blocks of 4 to ensure equal allocation to intervention and control groups. Participants, but not study staff or investigators, will be blinded to study group participation.

The primary outcome is completion of self-administered STI screening between the baseline and 3-month study visit. Based on prior research, we estimate that 20–25% of the control group will complete STI screening [12]. We anticipate POFG will increase STI screening by at least 50% (i.e. relative risk of 1.5 comparing the proportion completing STI screening in the intervention group to the control group). Given these assumptions, retention rates from past RCTs conducted by the study team within the target population, a two-sided alpha of 0.05 and 80% power, we will enroll a total of 450 participants (225 in each arm) to sufficiently power the trial.

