### Statistical analysis

Study hypotheses will be tested using an “intent to treat” analysis. Baseline characteristics will be compared between groups using chi-square tests for binary or categorical outcomes, and Wilcoxon rank-sum tests for continuous outcomes. For the primary outcome of STI screening uptake, the proportion of participants completing screening (i.e. returning a test to study staff) by the 3-month study visit will be compared across groups using a chi-square test or log-binomial regression if participant characteristics are found to vary at baseline between groups. For all analyses, participants who drop-out during the study and don’t provide at least 3-month follow-up data will be removed from the analysis. If at 3- or 6-months follow-up the POFG intervention shows efficacy for increasing STI screening uptake, we will conduct mediation and moderation analyses to explore what factors may be impacting the efficacy of POFG to change STI screening behavior.

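### 225 per arm does not give the stated 80% power over most of the assumed control range: 69% at 20% uptake, and under 5% room for loss even at 25%

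*Protocol article*

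**What the plan says.** The section on participant randomization and study sample size gives every input except retention:

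- Control uptake: "we estimate that 20–25% of the control group will complete STI screening".
- Effect: "relative risk of 1.5 comparing the proportion completing STI screening in the intervention group to the control group", described as the least improvement expected.
- Error rates: "a two-sided alpha of 0.05 and 80% power".
- Loss: "retention rates from past RCTs conducted by the study team within the target population" are said to have been taken into account, without a figure.

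From these it concludes that "we will enroll a total of 450 participants (225 in each arm) to sufficiently power the trial".

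The Statistical analysis section compares the proportions screened by 3 months with a chi-square test, or with log-binomial regression if the groups differ at baseline. It also states: "For all analyses, participants who drop-out during the study and don’t provide at least 3-month follow-up data will be removed from the analysis".

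**The concern.** This is the only power statement for the primary outcome, and it can be checked against its own inputs. A sample size offered for a range of control rates should hold at the unfavourable end of that range, or the text should say that it holds only at the other end. At a fixed relative risk, a lower control rate means a smaller absolute difference, so 20% is the demanding case.

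If 225 per arm is too few there, a null result could be taken as evidence from a trial with a 20% chance of missing the planned effect when the true chance is considerably higher. Removing dropouts from the analysis makes this worse, because the number that matters is the number analysed and not the number enrolled.

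**Working it through.** **Inputs** (all from the sample-size section): control proportion p₁ from 0.20 to 0.25; p₂ = 1.5 × p₁; two-sided alpha 0.05 (z = 1.960); power 80% (z = 0.842); 1:1 allocation; 225 per arm enrolled.

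**Required number per arm.** The pooled-variance formula, which matches an uncorrected chi-square test, with p̄ the mean of p₁ and p₂, is

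n = [1.960 × √(2p̄(1−p̄)) + 0.842 × √(p₁(1−p₁) + p₂(1−p₂))]² / (p₂ − p₁)²

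- 20% vs 30%: (1.2002 + 0.5119)² / 0.10² = 293.2, so 294.
- 22.5% vs 33.75%: (1.2462 + 0.5309)² / 0.1125² = 249.5, so 250.
- 25% vs 37.5%: (1.2848 + 0.5466)² / 0.125² = 214.7, so 215.

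The plan's 225 is therefore not reproduced at 20% or at the midpoint. It is approached only at 25%, with almost nothing left for retention.

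**Power with 225 per arm analysed.** Power = Φ{[(p₂ − p₁)√225 − 1.960 × √(2p̄(1−p̄))] / √(p₁(1−p₁) + p₂(1−p₂))}

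- 20%: Φ[(1.500 − 1.2002)/0.6083] = Φ(0.493) = 68.9%.
- 22.5%: Φ[(1.6875 − 1.2462)/0.6308] = Φ(0.699) = 75.8%.
- 25%: Φ[(1.875 − 1.2848)/0.6495] = Φ(0.909) = 81.8%.

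Exact enumeration of the uncorrected chi-square test gives 69.3%, 76.1% and 81.9%. Setting power to 80% and solving for p₁ gives 24.2%. So (24.2 − 20)/(25 − 20), or about 84% of the stated range, falls short with no loss at all.

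**Room for loss at 25%.** 1 − 215/225 = 4.4%, or 1 − 214.7/225 = 4.6% with n unrounded.

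**Effect of loss.** The document gives no retention rate, so these rates are assumptions for illustration.

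| Retention (assumed) | Analysed per arm | Power at 20% | Power at 22.5% | Power at 25% |
|---|---|---|---|---|
| 100% | 225 | 69% | 76% | 82% |
| 90% | 202.5 | 64% | 71% | 78% |
| 80% | 180 | 59% | 66% | 73% |

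**Relative risk detectable with 80% power.** With no loss: 1.58 at 20% and 1.49 at 25%. At 80% retention: 1.65 and 1.55.

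**Does another method rescue the figure?** At 20% control uptake with 225 per arm, the unpooled, arcsine and log-relative-risk versions give 69.4%, 69.2% and 67.6%. An exact calculation with continuity correction gives 65.1%. Only a one-sided 0.05 test comes close (79.1%, with no loss), and the section specifies a two-sided test.

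**The case against.** The strongest reply is that 25% lies inside the stated range, and there 225 per arm does give 82% power. The section does not expressly promise 80% at every control rate. This stands as far as it goes: the figure is right at the top of the range with almost complete retention. But the text offers 450 for 20–25% after allowing for retention, and that claim fails over most of the range before any loss.

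Second, the article condenses a fuller protocol, and the retention rate may be given there. That is fair, and its absence is not counted as a fault here. The main error needs no retention figure, because at 20% the number fails with everyone retained. The 90% and 80% rows are illustration only.

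Third, the tolerable loss at 25% depends on the formula: 1.0% with the log-relative-risk version, 5.8% unpooled, and none with continuity correction. The under-5% statement belongs to the formula that matches the planned test. All versions leave very little room.

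Fourth, the relative risk of 1.5 is presented as a minimum, and the detectable 1.49–1.58 with no loss is not far from it. A larger true effect would indeed give more power. Still, 1.5 is the effect the section uses for design, and the power claim has to be judged at that value.

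**Conclusion.** The power statement is wrong as written. For the design effect and a two-sided 0.05 chi-square test, 225 per arm gives 69% power at 20% control uptake and 82% at 25%. It reaches 80% only from about 24.2% upward, with no loss. The chance of missing the planned effect is 31% to 18% across the stated range with full retention, and 41% to 27% if retention were 80%, against the 20% implied.

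The full-retention figures rest only on inputs stated in the document. Those with attrition rest on assumed retention rates and on the stated rule of removing participants without 3-month data.

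**What to change.** Keep 450 and replace the power claim with what it provides, for example: 225 per arm gives 69% power at a control rate of 20% and 82% at 25% to detect a relative risk of 1.5 (two-sided 0.05) if all randomised participants are analysed; the relative risk detectable with 80% power is 1.58 at 20% and 1.49 at 25%. State the retention rate assumed and give the corresponding power for the number expected to be analysed.

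If kit return, which study staff record, were analysed for everyone randomised, dropout would no longer reduce the analysed number. The figures above would then apply provided that the 20–25% rate and the relative risk of 1.5 describe all randomised participants. If they describe only those followed up, counting non-returners as unscreened could lower both proportions, and power with them. The correction of the power statement does not depend on this change.

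The cost is a less favourable statement in the protocol. No participants, visits or tests are added.

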### Intervention

Protecting Our Future Generation (POFG) is a self-care intervention rooted in Asset Theory [17–25]. POFG provides participants with an opportunity to assess their own sexual risk and protective behaviors, understand their personal risk for current or future STI infection, receive tailored strategies and recommendations to engage in protective sexual health practices, and motivate completion of non-clinic based STI screening. The self-assessment includes questions pertaining to sexual health risk and protective behaviors and a valid clinical prediction tool established to predict STI positivity [16]. The personalized messaging describes key steps the person can take to lower their risk for STIs. The quiz with resulting score and personalized messaging will take approximately ten minutes to complete and be delivered via tablet at the first study visit. POFG participants will be offered a self-administered, non-clinic based STI testing kit (for *Neisseria gonorrhea*, *Chlamydia trachomatis* and *Trichomonas vaginalis*) after receiving their personalized messages.

### Control condition

The control program includes: a) a brief self-assessment (also called ‘quiz’), b) quiz score, and c) personalized messaging. For the control condition, the quiz, score and messaging will pertain to consumption of water, soda and sugar sweetened beverages. There will not be a comparable clinical prediction tool in the quiz for the control condition. However, based on the answers given on the control quiz, key steps the control participant can take to meet the recommended daily intake of water and sugar sweetened beverages will be delivered. The control quiz with resulting score and personalized messaging will take approximately ten minutes to complete and will be delivered via tablet at the first study visit. Control participants will also be offered a self-administered, non-clinic based STI testing kit (for *Neisseria gonorrhea*, *Chlamydia trachomatis* and *Trichomonas vaginalis*) after receiving their personalized messages. The content and structure of the control condition was recommended by the local study team from the participating tribal community and endorsed as a beneficial comparison to the intervention.

The quality of both programs (intervention and control) will be ensured through self-administration via tablet. Thus, delivery of each quiz and corresponding messaging is standardized across participants in each group.

### STI treatment

For participants who opt to take the STI testing kit (intervention or control) they can: 1) complete it and return it to a study staff immediately, 2) take the test with them, complete it at a later time and drop it off at the designated study office, or 3) complete it at a later time and coordinate with a study staff to have it picked up at a location they choose.

All participants (intervention and control) who test positive for a STI will receive an assisted referral to a Public Health Nurse at IHS with whom we have partnered on this study to ensure all participants who test positive for one or more STIs receive timely and high-quality treatment.

### Measures

The following assessments will be completed by participants: the standardized *Youth Health Risk Behavior Inventory* which has been previously adapted and piloted with Native American youth and young adults yielding Cronbach’s alphas ranging from 0.74–0.93; and the standardized *Youth Asset Survey*, with established reliability and validity among a random sample of 1350 youth (10% of which were Native; Cronbach’s alpha > 0.61) [17, 27, 28]. These two self-report surveys will collect information on participant demographics, sexual risk and protective behaviors, including STI screening uptake, as well as psychosocial assets and resources. All survey items were piloted with ten youth and young adults from the participating community (3 males and 7 females) ranging in age from 14 to 24 years; edits were made as necessary. See Table 1 for a complete description of measures.

**Table 1 Tab1:** Protecting Our Future Program Evaluation Measures

Measures	Description of Measure
Youth Health Risk Behavior Inventory	Assesses sexual behavior and related risk factors through close-ended questions that asks about STI and sexual behavior history, knowledge, intentions and attitudes. Adapted from Stanton and colleagues [27].
Youth Asset Survey	Assesses youth assets (knowledge, attitudes, future aspirations, use of time, health practices and responsible choices (role models, communication with parents and adults, community involvement and access to health care). Adapted from Oman and colleagues [17].

### Study visits and data collection

Data will be collected at baseline, 3 months, and 6 months post-intervention completion. At each study visit, participants will complete the aforementioned surveys. Data will be collected via tablets using REDcap (Research Electronic Data Capture) electronic data capture tools hosted at JHU [29]. REDCap is a secure, web-based application designed to support data capture for research studies, providing 1) an intuitive interface for validated data entry; 2) audit trails for tracking data manipulation and export procedures; 3) automated export procedures for seamless data downloads to common statistical packages; and 4) procedures for importing data from external sources. Participants will receive $30, $30 and $45 gift cards after completion of the baseline, 3- and 6-month post-intervention evaluations, respectively.

### Outcomes

#### Primary outcome

Completion of STI screening between the baseline and 3-month study visit is the primary outcome for this study.

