## Methods/design

### Study overview and hypotheses

We will conduct a two-arm randomized controlled trial (RCT) to test the efficacy of the POFG self-care intervention for impacting participant uptake of STI screening, in comparison to a control group. POFG includes a brief self-assessment to predict absolute STI risk and corresponding personalized messaging. We hypothesize participants who receive POFG will have a higher rate of STI screening completion at 3-months follow-up, compared with participants who receive the control program. We will measure STI screening uptake at 6-months follow-up to see if any increases were maintained over time. We hypothesize that POFG will increase protective behaviors among participants by: i) helping youth and young adults gain knowledge of their own sexual health risks, assets and resources; ii) motivating protection of those assets and resources; and iii) encouraging good health practices and making responsible choices. We hypothesize the effects of POFG on STI screening uptake will be mediated by participant’s substance use and past STI infection. See Fig. 1 for an illustration of the flow of participants through the study.

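### The primary outcome closes at the 3-month study visit rather than a fixed day from baseline, so time to succeed and inclusion both depend on attendance

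*Protocol article*

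**What the plan says.** Three sections of the protocol article set the primary outcome period, and all end it at a visit.

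- Primary outcome: "Completion of STI screening between the baseline and 3-month study visit is the primary outcome for this study".
- Participant randomization and study sample size: "The primary outcome is completion of self-administered STI screening between the baseline and 3-month study visit".
- Statistical analysis, which also says what completion means: "completing screening (i.e. returning a test to study staff) by the 3-month study visit will be compared across groups".

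The hypothesis names the time point more loosely, as a "higher rate of STI screening completion at 3-months follow-up, compared with participants who receive the control program". The schedule is nominal: "Data will be collected at baseline, 3 months, and 6 months post-intervention completion".

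Under STI treatment, a participant who takes a kit may return it at once, or "take the test with them, complete it at a later time and drop it off at the designated study office", or "complete it at a later time and coordinate with a study staff to have it picked up at a location they choose". None of these routes requires the 3-month visit.

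The Statistical analysis section announces an intent-to-treat analysis, then states for all analyses that "participants who drop-out during the study and don’t provide at least 3-month follow-up data will be removed from the analysis". The randomisation section says that participants are blinded to group, while staff and investigators are not.

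**The concern.** The event being counted is the receipt of a kit by staff. It has its own date and can happen without any visit. Closing the count at a visit brings two post-randomisation variables into the endpoint.

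- **Visit timing.** If the closing point is the day the visit takes place, a participant seen late has longer to score a success than one seen early. The 3-month completion rate then has no single meaning.
- **Attendance.** A participant who drops out without 3-month data leaves the analysis, even if staff hold that person's kit. The outcome is known and is discarded, which is not an intent-to-treat analysis of this endpoint.

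If either variable differs between arms, the primary comparison can shift without any effect of the programme on screening.

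**Working it through.** **Inputs from the protocol article.** Control completion is 20–25%, the relative risk is 1.5, there are 225 per arm, and the test is two-sided at 0.05. The planned differences are 0.20 × 1.5 − 0.20 = 10 points and 0.25 × 1.5 − 0.25 = 12.5 points. The article gives no return curve and no spread of visit dates, so those below are assumptions. It has no figure of its own for the window to reproduce.

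**1. Constant return rate, calibrated to p at day 91.** F(d) = 1 − (1 − p)^(d/91).

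| p at day 91 | day 77 (2 weeks early) | day 119 (4 weeks late) |
|---|---|---|
| 25% | 1 − 0.75^(77/91) = 21.6% | 1 − 0.75^(119/91) = 31.4% |
| 20% | 1 − 0.80^(77/91) = 17.2% | 1 − 0.80^(119/91) = 25.3% |

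**2. 60% of returns on the day of the offer, constant rate afterwards.** F(d) = 1 − (1 − 0.6p) × [(1 − p)/(1 − 0.6p)]^(d/91). At day 119:

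- p = 25%: 1 − 0.85 × (0.75/0.85)^(119/91) = 27.8%, up 2.8 points.
- p = 20%: 1 − 0.88 × (0.80/0.88)^(119/91) = 22.3%, up 2.3 points.

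**3. A share f of returns within 14 days, constant rate afterwards, calibrated to p at day 90.** F(d) = 1 − (1 − fp) × [(1 − p)/(1 − fp)]^((d − 14)/76). At day 120:

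| p at day 90 | f = 80% | f = 90% |
|---|---|---|
| 20% | 21.5% | 20.8% |
| 25% | 26.9% | 26.0% |

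The gain is 0.8 to 1.9 points.

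**4. What a timing difference between arms would do.** Assume no true effect, a constant return rate and 225 analysed per arm. One arm closes at day 90 with proportion p, and the other closes g days later with proportion q = 1 − (1 − p)^((90 + g)/90). With δ = q − p, s0 the pooled standard error and s1 the unpooled one, the chance of rejection is 1 − Φ((1.96·s0 − δ)/s1) + Φ((−1.96·s0 − δ)/s1).

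| Gap g between arms | p = 20% | p = 25% |
|---|---|---|
| 0 days | 0.050 | 0.050 |
| 7 days | 0.065 | 0.069 |
| 14 days | 0.109 | 0.123 |
| 30 days | 0.304 | 0.364 |

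For scale, a 7-day mean gap arises if a quarter of one arm is seen 28 days late and everyone else is on time (28/4 = 7). The constant rate is the least favourable of the three curves, so the error under front-loaded returns would be smaller. With equal timing in both arms, the error stays at 0.05.

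**5. Attendance.** This part needs no arithmetic. Completion is a return to staff, so it is observed whether or not the participant answers a survey. The exclusion rule is tied to 3-month follow-up data. A participant who returned a kit at baseline and then dropped out therefore has a known success that is not analysed. One who dropped out without returning a kit has a known non-completion that is also not analysed. The direction of any resulting bias cannot be derived from the document.

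**The case against.** The strongest reply has four parts.

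- **The visit may mean the scheduled time point.** The text never says that the window closes on the day of attendance, and the hypothesis speaks only of 3-months follow-up. This stands as a possible reading. The section on study visits does use the word for occasions when participants complete surveys, so the actual visit is the natural reading. A primary endpoint should not leave the choice open.
- **Visit tolerances belong in the full protocol or SAP.** This is true, and their absence here is not the point. The point is a closing rule stated in three places. A visit window would limit the inequality but not remove it.
- **The arms are treated alike.** Schedule, gift cards, kit offer and return routes are the same, and participants are blinded. This stands: nothing in the document indicates that timing or attendance will differ by arm.
- **Most kits may come back early.** The kit is offered at the first visit, and immediate return is one of the three routes. If so, the window matters little, as steps 2 and 3 show.

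A reader might also infer two stronger points that the document does not support. One is that absentees get an open-ended window. Drop-outs without 3-month data are in fact removed. The closing date is unclear only for someone who misses the 3-month visit but stays in the study. The other is that attending gives an extra chance to hand in a kit. Hand-in at that visit is not among the listed routes.

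**Conclusion.** The point holds as a weakness in how the endpoint is fixed, not as a demonstrated bias. The closing rule depends on a visit although the event does not, and the exclusion rule discards known primary outcomes in conflict with the stated intent-to-treat analysis. Neither depends on any assumed return curve.

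The size does depend on assumptions. A 4-week delay adds 6.4 points to 25% under a constant return rate, and about 1 to 3 points if most kits come back early. Those are shifts for the people who are late. Setting them against the planned 10 to 12.5 points as a bias would require one whole arm to be late and the other on time. A reader might infer that the type I error is inflated. It is inflated only if timing or attendance differs by arm, which unblinded staff make possible and the document does not show.

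**What to change.** Define the primary outcome as a study kit received by study staff within a fixed number of days of the baseline visit, for example 91, with the day of the offer included. Take it from the dated receipt. Apply it to every randomised participant, whether or when the 3-month visit takes place, and count no receipt by that day as not completed. Use the same kind of fixed-day rule for the 6-month count.

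This means rewording the outcome in the Primary outcome, sample size and Statistical analysis sections, and amending the exclusion of drop-outs for this outcome. The exclusion can be considered separately for the survey outcomes, which do need a visit.

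The cost is small but not nil. The article does not describe a receipt log, so the team must confirm that receipt dates exist for every kit, including those from participants already enrolled. The change should be settled before outcomes are compared by arm. A few kits received after the cut-off would no longer count, and drop-outs without a receipt would enter the denominator, so the completion rates may be slightly lower.
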